### Training and support of practice nurses in the intervention arm

Intervention practice nurses and GPs will receive a two-hour training session before starting the trial, consisting of a brief introduction to the SeMaS, demonstration of a consultation with a SeMaS report and skills practice using role play. The practice nurses will be specifically instructed on the options for personalized self-management support, such as the creation of individual care plans, options to influence the barriers for self-management, and the referral to self-management interventions. During the training, the practice nurses will receive a manual that indicates which profiles are suitable for self-management, which are suitable with minor barriers, and which are unsuitable for self-management at this time. The manual also contains the instructions for personalized self-management support.

Subsequently, intervention practices will be visited to provide further support in working with the SeMaS. The user manual and examples of reports with suggestions for personalized self-management support will be discussed.

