### Self-management support

During the study period, practice nurses of the intervention arm will receive a report with the profile of the patients who filled in the questionnaire. Patients will also receive tailored feedback. Practice nurses are instructed to adjust the delivery of care to the profile. For each factor the manual provides advice to help support the patient in case of a barrier. For example, when a patient experiences low social support, the practice nurse and the patient search for additional social support, or find ways to cope with this low support. For a patient with low self-efficacy, the advice is to set a goal with the patient with a high chance of success, to foster the self-efficacy. When patients show major barriers for self-management, the manual gives instruction and support for the practice nurse to work on this barrier before starting with self-management activities.

When no barrier is present, the practice nurse is advised to create an individual care plan with the patient, and refer to the self-management interventions, if applicable. Also, the manual contains a card with the possible self-management interventions, categorized by the skills that are asked about in the SeMaS questionnaire (computer, group, self-care). The manual was developed by the research team and reviewed by the stakeholders group. The advice was based on the method of actual practice and maintenance, which is used in the care group.

Control practices will deliver care as usual, and will receive the training one year later. Care as usual may include the use of an individual care plan or referral to the self-management interventions, as this is available for the entire care group. Patients will be invited in the same inclusion period as in the intervention arm. They will be asked to fill in the questionnaire, without feedback to themselves or their practice nurse.

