### Outcomes

The primary outcome is the difference in patient activation score between baseline and six months between the intervention and control arm, using the PAM-13 [23]. The PAM-13 is an interval-level, uni-dimensional, Guttman-like measure. In the study of Greene and Hibbard the average PAM score was 66.4 (SD 15.4; n = 25,047) [34].

We expect that using the SeMaS instrument will lead to more effective self-management support. Also, we expect that patients will adhere better to the self-management interventions, as they are referred based on the SeMaS profile. To measure whether the self-management support is more successful in the intervention arm than in the control arm, we will perform medical-record data analysis. The outcome measures include the number of completed individual care plans, the number of patients performing self-monitoring, the number of referrals to self-management interventions (group courses and internet coaches), and adherence to these interventions, the number of referrals to informative websites, and the number of consultations in the general practice and emergency care in the study period. We will assess how these data relate to the results on the SeMaS questionnaire at baseline.

Furthermore, we expect that patients who receive personalized self-management support, will be more able to improve their lifestyle than patients receiving care as usual. Lifestyle factors will be measured with the rapid assessment of physical activity (RAPA) and the rapid eating assessment for participants-short (REAP-S) [35,36]. Smoking behavior will be measured with the 10-item Behavior Change Consortium questionnaire [37]. The difference in the score per lifestyle behavior between baseline and time (T)1 will be calculated to assess the change in lifestyle behavior. The secondary outcome measures are defined as the difference in the average score between control and intervention at T0 and T1 for the RAPA and REAP-S questionnaires. For smoking, the outcome is defined as the difference between the numbers of patients smoking in the control and intervention arms at T0 and T1.

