We will also perform a per protocol analysis of data from patients who received a referral to a self-management intervention. We will examine adherence to the self-management intervention program, comparing patients from intervention practices with control. Also, we will test the effect of the intervention on process outcomes (filled in individual care plans, the number of referrals to self-management interventions, and the number of consultations in the general practice and emergency care) using multilevel multivariate regression techniques.

The effect of cluster will be determined by performing a multilevel regression analysis without explaining variables. With this analysis, we can determine the variance at the different levels. Subsequently, we can determine the intraclass correlation of this study:

ICC=Clustervariance/Clustervariance+Patients'variance

We will qualitatively analyze the interviews with healthcare professionals. The interviews will be transcribed verbatim. The transcripts will be analyzed by open coding at macro level using predefined main codes according to the barriers and facilitators at different levels of healthcare, as proposed by Grol and Wensing [38]. These levels are: innovation, individual professional, patient, social context, organizational structure, and economical and political context. After the open coding, the research team will group themes and subthemes for each level of healthcare. The program Atlas.ti (version 6, ATLAS.ti Scientific Software Development GmbH) will be used for analysis.

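### The per-protocol and adherence comparison conditions on referral, which the intervention itself steers, so it is not a randomised comparison and the label does not fit

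*Protocol article*

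**What the plan says.** After the primary and secondary analyses, the Analysis section adds: "We will also perform a per protocol analysis of data from patients who received a referral to a self-management intervention". The next sentence reads: "We will examine adherence to the self-management intervention program, comparing patients from intervention practices with control". The same paragraph lists process outcomes on which the intervention's effect will be tested, including "the number of referrals to self-management interventions, and the number of consultations in the general practice and emergency care".

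Referral is part of the intervention. The section on training and support of practice nurses lists, among the forms of support that intervention nurses are instructed in, "options to influence the barriers for self-management, and the referral to self-management interventions". Under Self-management support the manual's advice depends on the profile. For patients without barriers: "When no barrier is present, the practice nurse is advised to create an individual care plan with the patient, and refer" (the sentence goes on to limit this to cases where it applies). For patients with major barriers the manual helps the nurse "to work on this barrier before starting with self-management activities". In control practices, "Care as usual may include the use of an individual care plan or referral to the self-management interventions", but neither nurse nor patient sees the SeMaS result.

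The Outcomes section lists adherence among the medical-record measures and gives the hypothesis: "we expect that patients will adhere better to the self-management interventions, as they are referred based on the SeMaS profile".

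**The concern.** A comparison between arms is protected by randomisation only if membership of the analysed set does not depend on what happened after allocation. Here it does. Whether a patient is referred is decided at or after the consultation, by a nurse whose rule for referring differs by arm. Equal referral rates would not repair this, because the kind of patient referred could still differ.

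The selection is also tied to the outcome. The profile covers aspects such as self-efficacy, social support, coping style and depression, which the developers chose because they bear on the chance of successful self-management. Sorting patients on them before referral is likely to sort them on adherence.

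At stake is the adherence hypothesis. Among referred patients, two explanations of a difference cannot be separated: that a given patient adheres better with profile-based support, or that different patients were referred.

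The label adds a second problem. Readers take a per-protocol set to mean patients treated as planned. This set can leave out intervention patients handled as the manual directs, and it takes in control patients referred under usual care.

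**Working it through.** **Figures in the protocol.** There is none to reproduce: no referral rate, adherence rate or size is given for this analysis. The calculations below use assumed values and show only that a difference can arise, and how its sign depends on the referral rules.

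**Step 1: two groups, no true effect.** Assume 40% of patients have no barrier and 60% have one, and that adherence once referred is 70% and 40% respectively, the same in both arms. With referral probabilities r0 (no barrier) and r1 (barrier),

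adherence among referred = (0.4·r0·0.70 + 0.6·r1·0.40) / (0.4·r0 + 0.6·r1).

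- Control refers both groups alike (r0 = r1): 0.4·0.70 + 0.6·0.40 = 52%.
- Intervention, r0 = 0.50, r1 = 0.10: (0.140 + 0.024) / (0.20 + 0.06) = 0.164 / 0.26 = 63%. Difference from control: +11 points.
- Intervention, r0 = 0.40, r1 = 0.20: (0.112 + 0.048) / (0.16 + 0.12) = 0.160 / 0.28 = 57%. Difference: +5 points.
- If control nurses happened to refer at 0.50/0.10 and intervention nurses at 0.40/0.20, the same formula gives 57% against 63%, or -6 points.

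**Step 2: continuous readiness, no true effect.** Readiness is standard normal, and adherence rises with it (logit slope 1 per SD). Referral either depends on readiness (logit slope 1 per SD) or is unrelated to it. Differences are unadjusted.

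| Intervention referral | Control referral | Adherence among referred | Difference |
|---|---|---|---|
| 20%, by readiness | 20%, unrelated | 64% v 50% | +14 |
| 40%, by readiness | 20%, unrelated | 60% v 50% | +10 |
| 40%, by readiness | 20%, by readiness | 60% v 64% | -4 |
| 40%, by readiness | 10%, by readiness | 60% v 67% | -6 |
| 20%, unrelated | 20%, unrelated | 50% v 50% | 0 |

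The first row has equal referral rates and still gives the largest difference. Rows three and four use the same slope in both arms, and the sign reverses because the arm that refers more reaches further down the readiness scale.

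**Step 3: the all-enrolled outcome on the Step 1 values.** The proportion both referred and adherent is the numerator of the formula: 16.4% with intervention referral at 0.50/0.10. If control refers 20% of everyone, it is 0.20 × 52% = 10.4%. The 6-point gap is a real effect of allocation, but it comes wholly from how many and which patients were referred (26% against 20%). This outcome must therefore be read with the referral outcome.

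**Step 4: within barrier group.** In Step 1 the comparison is 70% v 70% and 40% v 40%. Stratifying removes the difference there because barrier status is, by construction, the only thing that selects.

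**The case against.** *It is only an additional analysis.* This stands. The primary PAM-13 analysis is by intention to treat, and the process outcomes are not restricted to referred patients. A reader might infer that the trial's main result is compromised; nothing in the article supports that.

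*The direction is not established.* This also stands. A reader might infer that the restriction must favour the intervention. That requires control nurses to refer regardless of barriers, which the article does not say. GPs and nurses across the care group were trained in motivational interviewing and person-related factors, so control nurses may also refer readier patients.

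*PAM-13 in this set.* A reader might infer a biased PAM-13 comparison as well, but adherence is the only outcome named beside this set.

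*Selection is the mechanism.* Referring suitable patients, and matching programmes to skills, is what SeMaS is for. Higher adherence among the referred can fairly describe better-targeted referral. It cannot show that the same patient adheres better, so this argues for relabelling the comparison rather than removing it.

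*Baseline SeMaS is measured in both arms, and the Outcomes section plans to relate process data to it.* This helps, and the figures above ignore it. But no adjusted arm comparison is promised. The covariates in the Analysis section are given for the secondary outcomes and, of the SeMaS aspects, include only social support, plus a recorded depression diagnosis. Adjustment would not deal with selection on unmeasured traits.

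*The text is partly implicit.* The adherence sentence states no denominator; restriction to referred patients follows from what adherence means. A patient with a major barrier is not barred from later referral, so exclusion is possible rather than certain. The article gives only an outline of the analysis plan, but it does itself fix the set, the comparison and the label.

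**Conclusion.** The point holds as a minor to moderate one. As described, the analysis compares arms in a set formed after randomisation by a process that the intervention is designed to change, under a label that does not describe the set. A difference in adherence of either sign could appear with no effect on any patient. The range found, about -6 to +14 points, rests on assumed referral and adherence rates and on unadjusted comparisons. It shows that the problem can be material; it does not estimate the bias in this trial. The conclusion needs only that the referral rule differs between arms in a way related to adherence, which the manual's advice and the stated hypothesis both make likely.

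**What to change.** 1. Define the adherence outcome as referred to and adherent with a self-management intervention, counting patients who are not referred as not having the outcome. Analyse it over all enrolled patients by allocated arm, in a multilevel logistic model with practice as cluster, and report it beside the planned referral outcome.
2. Keep adherence among referred patients as a descriptive comparison, stated to be non-randomised. Show it by, or adjusted for, baseline SeMaS barrier category; the Analysis section already defines three such categories.
3. Drop the label per protocol for the referred-patient set.

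The cost is a changed denominator and some wording. The medical-record data are the same, and the Trial status section says patients were still being recruited at submission. The downside is that the all-patient proportion is lower and mixes referral with adherence. It should therefore sit beside the referral result and the descriptive adherence figure, not replace them.

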### Sample size

Sample size calculations have been made using the results from three studies on the primary outcome measure, PAM-13 [17,34,39]. In these studies, improvements in PAM scores after intervention vary from 4% to 8% (SD 12 to 17). Based on these studies, we expect to find a difference in PAM score of 6% (SD 14.0) in this study. For the power calculations, we assume an intraclass correlation coefficient (ICC) of 0.05 based on the article of Campbell *et al*. [40]. This article states that an ICC of 0.0 to 0.5 is normal for outcomes in primary care research. To reach a power of 80% and alpha of 0.05, and considering ICC of 0.05, at least 25 patients per practice are needed when using 15 practices. With an expected dropout rate of 33%, 33 patients would be needed per practice, thus, 495 in total. Our secondary outcomes comprise lifestyle measures that will not be applicable to every patient, such as smoking. Therefore, we strive to include 50 patients per practice. Thus, 750 patients will be included in total.

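### The trial's ICC is to come from a model without a trial-arm term; if that model is fitted to follow-up or change scores, any intervention effect is counted as clustering

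*Protocol article*

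**What the plan says.** In the protocol article, the Analysis section says: "The effect of cluster will be determined by performing a multilevel regression analysis without explaining variables". This model is to separate the variance at the different levels, after which "Subsequently, we can determine the intraclass correlation of this study", by the formula "ICC=Clustervariance/Clustervariance+Patients'variance" (read as cluster variance divided by the sum of cluster and patient variance). The text does not say which outcome or which measurement time the model uses. It mentions no ICC from a model that contains trial arm.

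The primary analysis is described separately in the same section: a multilevel linear regression of the follow-up score with the baseline score as covariate.

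The Sample size section gives the planning values: "we assume an intraclass correlation coefficient (ICC) of 0.05", and "we expect to find a difference in PAM score of 6% (SD 14.0) in this study". It concludes that "at least 25 patients per practice are needed when using 15 practices". Under Practices, randomisation is by whole practice, and the columns of Table 1 add up to 7 intervention practices (2+1+2+2) and 8 control practices (1+3+2+2).

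**The concern.** Arm is constant within a practice. A model with no explanatory variables has only one place for a difference between intervention and control practices, namely the between-practice variance. The ICC formula would then count the treatment effect as clustering.

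The ICC that enters a design effect describes how much practices differ within an arm. That is the meaning of the 0.05 in the Sample size section. An empty-model ICC from follow-up data over both arms is a different quantity, and it rises with the effect of the intervention. Set beside 0.05, it could make clustering look worse than planned. Anyone who used it to size another trial would ask for too many patients.

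**Working it through.** **Inputs.** Difference 6, SD 14.0 (total variance 196), ICC 0.05, 80% power, alpha 0.05, 25 evaluable patients in each of 15 practices (Sample size section); 7 v 8 practices (Table 1). The protocol does not state sidedness; two-sided is taken.

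**1. Reproduce the plan's figure.** Per arm without clustering: 2 × 196 × (1.960 + 0.842)² / 6² = 85.5. Design effect at 25 per practice: 1 + 24 × 0.05 = 2.20. Total: 2 × 85.5 × 2.20 = 376, against 15 × 25 = 375. The plan's 25 per practice is reproduced, with the 6% taken as 6 PAM points. If it meant 6% of the cited mean of 66.4, which is 4.0 points, power at 25 × 15 would be only about 46%. Six points is therefore the planning value.

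**2. Variance components at the planning values.** Between practices within an arm: 0.05 × 196 = 9.8. Within practices: 196 − 9.8 = 186.2.

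**3. What an empty model adds on follow-up or change scores.** With an effect δ, the arm difference adds δ² × (7 × 8)/(15 × 14) to the sample variance of the 15 practice means. With divisor 15 × 15 (maximum-likelihood style) it adds slightly less. For δ = 6:
- 36 × 56/210 = 9.60, so ICC = (9.8 + 9.60)/(196 + 9.60) = 19.40/205.60 = 0.094
- 36 × 56/225 = 8.96, so ICC = 18.76/204.96 = 0.092

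Either is 1.8 to 1.9 times the within-arm value of 0.05.

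**4. Simulation check.** 40,000 trials of 15 equal-sized practices, 7 v 8, with a one-way variance-components estimator truncated at zero:

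| Model and effect | Mean ICC (25, 33 or 50 per practice) |
|---|---|
| Empty model, 6-point effect | 0.093 |
| Arm in the model, 6-point effect | 0.049 to 0.050 |
| Empty model, no effect | 0.049 to 0.050 |

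**5. Sensitivity of the expected empty-model ICC** (range over the two divisors; effects of 4 and 8 are the ends of the range in the Sample size section):

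| True ICC | Effect | Empty-model ICC | Ratio |
|---|---|---|---|
| 0.05 | 4 | 0.069 to 0.070 | 1.4 |
| 0.05 | 6 | 0.092 to 0.094 | 1.8 to 1.9 |
| 0.05 | 8 | 0.121 to 0.126 | 2.4 to 2.5 |
| 0.02 | 6 | 0.063 to 0.066 | 3.1 to 3.3 |
| 0.10 | 6 | 0.139 to 0.142 | 1.4 |

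The two practices that share a nurse were randomised together. Counting them as one unit (7 v 7 or 6 v 8) gives 0.094 to 0.095 at the planning values, so this does not matter here.

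**6. Baseline scores.** Baseline PAM-13 carries no intervention effect, so δ = 0 and the added term is zero. An empty model is then adequate.

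**The case against.** The strongest reply is that the text never says the empty model uses follow-up data. PAM-13 is also measured at baseline, where nothing is inflated, and the section calls itself an outline of a fuller analysis plan. This stands as a limit: the bias is conditional. It does not remove the point. The article positively prescribes a model without explanatory variables for the ICC of this study, within a section on intervention effects, so follow-up or change is a natural reading and needs to be excluded or corrected.

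Second, no result depends on this ICC. The primary, secondary and process outcomes have their own multilevel models, and the plan uses the empty-model ICC in no test, correction or decision. This stands in full. A reader might infer that the primary effect estimate or p-value is compromised; the documents do not support that.

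Third, the harm downstream is inferred. The documents do not say that the observed ICC will be compared with 0.05 or offered for planning. For illustration, a later trial with 25 per cluster that adopted 0.094 would use a design effect of 1 + 24 × 0.094 = 3.26 instead of 2.20, or 48% more patients. Both the adoption and the cluster size are assumptions.

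Fourth, 15 practices estimate any ICC poorly. With arm in the model, the simulated 95% range at a true ICC of 0.05 is about 0 to 0.12 with 25 per practice, and 0.01 to 0.11 with 50. A single estimate of 0.09 would not show that the trial was under-designed. This is a reason to report an interval. It does not excuse a systematic upward shift.

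**Conclusion.** The point holds in conditional form. If the empty model is fitted to 6-month or change scores over both arms, the reported ICC is biased upwards whenever the intervention has an effect: about 0.09 instead of 0.05 at the planning values.

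It is tempting to say that the ICC will nearly double. The documents do not support that as a general statement. It requires follow-up or change data, a true ICC of 0.05 and the full 6-point effect; other combinations in the table above give ratios from 1.4 to 3.3, and with no effect the ratio is 1.

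The consequence is confined to a descriptive statistic and to whatever use is later made of it. The calculation further assumes equal practice sizes and the planning SD of 14.

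**What to change.** Either of two one-line changes settles it:
- Name the outcome and time point, and estimate the ICC of the follow-up outcome from a multilevel model with trial arm as a fixed effect. A confidence interval is advisable with only 15 practices.
- Or state that the empty model is fitted to baseline PAM-13 only.

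REML estimation, stratification factors as fixed effects and an additional baseline-adjusted ICC are optional; they do not follow from the error shown. The cost is one sentence in the analysis plan and at most one extra model fit. No new data are needed, and the primary analysis does not change.
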